#### Adverse events (AEs) and adverse events of special interest (AESIs)

AEs are defined as any undesirable experience occurring to a subject during the study, whether or not considered related to the TEAM experimental arm.

A number of toxicities are so well-known and frequent during conventional 6MP/MTX maintenance therapy that they are to be expected and will not be considered AEs, and will not be reported routinely to the national regulatory authorities or the DSMC.

These include:Myelosuppression. Since this is the target of maintenance therapy, leucopenia and thrombocytopenia will not be regarded as an AE. This includes febrile neutropenia leading to hospitalization.A rise in ALT with normal liver function tests (i.e., bilirubin and INR (or factor II-VII-X)).A rise in bilirubin to less than 5 x UNL, except when SOS is diagnosed (if patients experience ALT at least 3 x UNL with bilirubin 2 x UNL within the first 3 months of maintenance therapy this will be reported).A decrease in coagulation factors II-VII-X.A rise in amylase of less than 5 x UNL.

Most of the toxicity-reporting will be carried out by the reporting of 23 predefined AESIs via the ALLTogether1 eCRF-system at specified time points defined by risk group. Most of these toxicities will not be reported as SAEs.

AESIs specifically related to TEAM are:Symptomatic osteonecrosisLiver failure with encephalopathySOS/NRHHypoglycemia leading to hospital admission

In addition these toxicities will be collected at the same time-points as the AESIs:Incidence of ≥ grade 3 infectionsIgG levels and administration of IVIGALT and bilirubin elevations ≥ grade 3 (> 3 x UNL for bilirubin and > 5 x UNL for ALT)

In accordance with the ALLTogether1 protocol, expected AEs will not be reported for most of the study-period. However, for the first 12 weeks, AE-reporting will be more extensive:
All AEs ≥ grade 3 reported spontaneously by the subject or observed by the investigator or staff will be recorded from the start of maintenance for the first 3 maintenance blocks (= 12 weeks) except for non-reportable AEs:Alopecia, fatigue, anorexiaLaboratory abnormalities > grade 3 not considered to be clinically significant and/or responding to standard medical management

Abnormal laboratory findings without clinical significance (based on the investigator’s judgement) are not to be recorded as AEs. Clinical significance is defined as laboratory value changes that require clinical intervention or changes or adjustment in current therapy. Where applicable the clinical sequelae (not the laboratory abnormality) are to be recorded as the AE.

#### Serious adverse events (SAEs)

A serious adverse event is any untoward medical occurrence or effect thatresults in deathis life threatening (at the time of the event)requires hospitalization or prolongation of existing inpatients’ hospitalizationresults in persistent or significant disability or incapacityis a congenital anomaly or birth defect, orany other important medical event that did not result in any of the outcomes listed above due to medical or surgical intervention, but could otherwise have been based upon appropriate judgement by the investigator.

An elective hospital admission will not be considered as a SAE.

The investigator will report all SAEs to the sponsor without undue delay (within 24 h) after obtaining knowledge of the events. However, this applies only to the first 12 weeks of the maintenance phase for both the experimental- and the control arm.

In addition to the SAE-criteria listed above, suspected serious drug-induced liver injury (Hy’s law cases – described in Additional file 3), should also be reported within 24 h for the first 12 weeks.

From the 13th week of the maintenance phase until the end of therapy only SOS/VOD and NRH should be reported within 24 h of obtaining knowledge of the event.

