### Maintenance therapy

Maintenance therapy is initiated in treatment week 37 and continued in 4-week cycles until 2 years from complete remission (25 months/108 weeks from diagnosis) (Table 4). This duration is independent of the total cumulative administered number of days and drug doses. When initiating maintenance therapy, patients should fulfill the following criteria:Absolute neutrophil count (ANC) ≥0.75 × 10^9^/L (and not falling)Platelets ≥75 × 10^9^/L (and not falling)Serum creatinine ≤2 x the UNLAlanine aminotransferase (ALT) ≤ 3 UNLBilirubin ≤1.5 x UNLNo active systemic infection or evidence of hepatic SOSCardiac shortening fraction ≥30% or ejection fraction be ≥50% by echocardiography/MUGA

**Table 4 Tab4:** Mandatory examinations during maintenance therapy

Maintenance therapy week		0	4	8	12	24–36-48-etc
Timeline for standard and experimental arm	Screening d − 14 to 0	Start MT d1	2nd cycle MT d 29	3rd cycle MT d 57	4th cycle MT d 85	Every 12 weeks till end of maintenance
Informed consent^a^	X					
Medical History^b^	X	X	X	X		X
Physical Examination	X	X	X	X	X	X
Height, weight, BSA^c^	X	X	X	X		
Vital signs^d^	X	X	X	X		
Performance Status^e^	X	X	X	X		
Pregnancy test^f^	X		(X)	(X)	(X)	(X, monthly)
Echocardiogram	X^q^					X (end of MT)
Eligibility and registration^g^	X					
Concomitant Med	X	X	X	X	X	
Treatment						
LP with IT^h^				X		ALLTogether1
Maintenance therapy (6MP/MTX/6TG/VCR/DEXA)		Continuously				
Safety FU						
CBC and differential	X	X	X	X	X	X
Chemistry panel A^i^	X	X	X	X	X	
Chemistry panel B^j^						X
Amylase, Lipase	X			X		
Serum Ig levels^k^	X			X		X
Immunophenotyping of B-cells^l^		(X)			(X)	(X)
Adverse events	X	X	X	X	X	ALLTogether1
AESIs^m^	X	X	X	X	X	X
6MP/MTX metabolites^o^			X	X	X	X (monthly)
Efficacy FU						
Disease/survival status^p^		X			X	ALLTogether1

*BSA* body surface area, *CBC* complete blood count, *ECG* electrocardiography, *LP* lumbar puncture, *MRD* measurable residual disease, *IT* intrathecal therapy, *ALLTogether1* according to description in ALLTogether1 protocol

^a^ Informed consent must be obtained before any study specific investigations are performed Information can be handed out and consent can be obtained from treatment phase “IR-High Consolidation 2” onwards

^b^ Medical History including review of cancer diagnosis and previous cancer treatment (screening/pre-study visit only), current medications and any current medical conditions or abnormalities

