#### Developmental safety update report (DSUR)

In accordance with the ALLTogether1 protocol, the sponsor will submit a safety report to the NPI/CTU in the participating countries once a year throughout the clinical study, to enable them to report the DSUR to the accredited IRB/EC, and competent authorities of the participating countries.

This safety report consists of:A list of all suspected (unexpected or expected) serious adverse reactions, along with an aggregated summary table of all reported serious adverse reactions, ordered by organ system.A compilation of AESIs for the whole patient-population and the pooled patient-populations for the risk-groups and for the randomized studies.A report concerning the safety of the subjects, consisting of a complete safety analysis and an evaluation of the balance between the efficacy and the harmfulness of the interventions under investigation.

The data in the annual progress and safety report is aggregated without specification of randomized arms.

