#### Data safety monitoring board (DSMB)

The DSMB for the TEAM study will be the same as for the ALLTogether1 protocol. The DSMB periodically (at least annually) reviews safety and study data and makes recommendations based on their review along with assessing the performance of overall study operations and any other relevant issues, as necessary. The basis for the review is a report provided by the study statistician without the knowledge or influence by the sponsor, PI or steering committee. The DSMB will receive annual progress reports on patient recruitment, rate of events (relapse, DCR1 and SMN), occurrences of SOS, NRH, AESI, SAEs, SUSARs and levels of DNA-TG in the randomization arms.

The DSMB can recommend extension of the study to ensure adequate enrollment.

The advice of the DSMB will be sent to the sponsor of the study to be shared with the steering committee. Should the sponsor decide not to fully implement the advice of the DSMB, the sponsor will send the advice to the reviewing accredited competent authorities, including a note to substantiate why (a part of) the advice of the DSMB will not be followed.

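### After week 12 of about 71–72 maintenance weeks, the protocol gives no expedited route to the sponsor for a suspected unexpected serious reaction other than SOS/VOD or NRH, although the SUSAR, DSUR and DSMB duties continue

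*Protocol article*

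**What the plan says.** All references are to the protocol article.

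- **Serious adverse events (SAEs).** The general duty is "The investigator will report all SAEs to the sponsor without undue delay (within 24 h) after obtaining knowledge of the events". The next sentence restricts it: "this applies only to the first 12 weeks of the maintenance phase for both the experimental- and the control arm". Suspected serious drug-induced liver injury (Hy's-law cases) "should also be reported within 24 h for the first 12 weeks". After that: "From the 13th week of the maintenance phase until the end of therapy only SOS/VOD and NRH should be reported within 24 h".
- **Adverse events and AESIs.** General recording of grade 3 or higher AEs has the same window: "recorded from the start of maintenance for the first 3 maintenance blocks (= 12 weeks"). Most other toxicity comes through 23 predefined AESIs, entered in the eCRF at set time points. Infections of grade 3 or higher and ALT/bilirubin elevations of grade 3 or higher are collected alongside. This section presents the reduced reporting as a relief for expected AEs.
- **SUSARs.** The 7-day and 15-day deadlines run from the sponsor's first knowledge. No end date is given. Unexpectedness is judged against the product information.
- **Developmental safety update report (DSUR).** The yearly report, issued for the whole duration of the study, contains "A list of all suspected (unexpected or expected) serious adverse reactions".
- **Data safety monitoring board (DSMB).** Its annual reports cover "occurrences of SOS, NRH, AESI, SAEs, SUSARs and levels of DNA-TG in the randomization arms", among other items.

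**The concern.** A SUSAR deadline that starts when the sponsor learns of the event depends on someone telling the sponsor. Up to week 12 the SAE duty does that. From week 13 the text leaves two diagnoses on the 24 h duty, and the reference safety information for 6TG (Table 3) lists both as very common reactions. The only expedited stream left therefore carries events that are expected in kind; only unexpected severity could make one of them a SUSAR.

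The downstream duties are written as if the input continued. The regulator's yearly list is meant to hold every suspected serious reaction, and the DSMB is meant to see SAEs and SUSARs by arm. Followed as written, the SAE section does not supply these after week 12. It also does not match the AE section, which exempts expected events, whereas the SAE section makes no distinction between expected and unexpected.

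At stake is how quickly an unforeseen serious reaction to a new three-drug combination is noticed. The pilot had 34 patients, the oral suspension borrows the tablet SmPC, and early termination depends on the DSMB's toxicity review.

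**Working it through.** **Length of the reporting window.** Three blocks of 4 weeks: 3 × 4 = 12 weeks, which reproduces the plan's own figure.

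**Length of maintenance.** The Maintenance therapy section says "Maintenance therapy is initiated in treatment week 37 and continued in 4-week cycles until 2 years from complete remission (25 months/108 weeks from diagnosis"). As a check, 25 months × 365.25/12/7 = 108.7 weeks, consistent with the stated 108. The length itself is not stated and follows by subtraction:
- 108 − 37 = 71 weeks, or
- 108 − 36 = 72 weeks if week 37 is counted in full (72/4 = 18 complete cycles).

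**Share covered by the general SAE and Hy's-law duty.** 12/71 = 16.9%; 12/72 = 16.7%. The remaining 59 to 60 weeks (about 83%) have a 24 h duty for SOS/VOD and NRH only.

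**Time at the maximum 6TG dose inside the window.** The experimental-arm section starts 6TG at 2.5 mg/m²/day and adds 2.5 every 2 weeks: 2.5, 5, 7.5, 10 and 12.5 at weeks 0, 2, 4, 6 and 8. The maximum is reached at week 8 at the earliest, so at most 12 − 8 = 4 weeks at that dose lie in the window. The weeks then left in maintenance are 71 − 8 = 63 or 72 − 8 = 64; 4/63 and 4/64 are both about 6%.

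**Experimental-arm exposure outside the window.** With 778 patients and half on TEAM, n = 389. If all complete maintenance, exposure after week 12 is 389 × 59/52 = 441 to 389 × 60/52 = 449 patient-years. This is an upper bound, since some patients will stop early.

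**What still reaches the database after week 12.**

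| Route | Where stated | Seriousness or causality trigger, and deadline |
|---|---|---|
| SOS/VOD, NRH | SAE section; organ toxicities section | 24 h, by diagnosis |
| 23 AESIs; grade 3+ infections, ALT, bilirubin | AE section; Table 4 notes | Set time points; no trigger shown |
| Toxicities, and relapse, death in remission, SMN | Study procedures | As for the parent protocol; none shown |
| AE data registered continuously in the CRF | Recruitment and consent | None shown |

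Only the first row has a deadline. The last row has no time limit, which itself sits awkwardly with the 12-week limit on general AE recording.

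**Liver signals.** The AE section reports the combination of ALT at least 3 × UNL with bilirubin 2 × UNL only within the first 3 months. Later collection begins at ALT > 5 × UNL or bilirubin > 3 × UNL. As an illustration, a patient in week 20 with ALT 4 × and bilirubin 2.5 × UNL meets the early criterion and falls below both later thresholds. In the same section, a bilirubin rise under 5 × UNL is not counted as an AE unless SOS is diagnosed. The Hy's-law definition is in an additional file that is not shown, so this comparison uses only the thresholds in the article.

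**The case against.** What narrows at week 13 is the 24 h duty, not capture. AESIs are collected to the end of maintenance, deaths in remission are registered with cause, liver values are measured every 12 weeks, and SOS/VOD and NRH stay expedited throughout. The DSMB also sees relapse, death in remission, SMN, AESIs and DNA-TG levels. TEAM is a sub-protocol; the parent ALLTogether1 protocol is not shown and may contain a SUSAR route. The 12-week limit appears in more than one place and looks deliberate.

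Most of this stands, and it rules out three stronger readings that a reader might infer.

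- That late serious events have no reporting route at all. The continuing eCRF routes contradict this.
- That a SUSAR is unlikely to be among the AESIs because it is unexpected. Unexpectedness is judged against the SmPC, not the AESI list. Symptomatic osteonecrosis, liver failure with encephalopathy and hypoglycemia leading to admission are TEAM AESIs, yet Table 3 does not name them. Only the four TEAM-specific entries are shown, so what the full list misses cannot be known.
- That the unknown SOS incidence makes the gap worse. SOS is one of the two events that remain on 24 h reporting.

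The objection does not remove the conflict. None of the remaining routes is shown with a deadline or with a trigger for seriousness or causality. An unseen parent document may supply one, but it would then contradict a sentence here that admits only two diagnoses. An investigator reading this text would follow that sentence.

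**Conclusion.** The point holds as a conflict within the document. For about 83% of maintenance (59 to 60 of 71 to 72 weeks), the protocol states no expedited route by which a suspected unexpected serious reaction other than SOS/VOD or NRH reaches the sponsor, and it ends Hy's-law notification. The SUSAR deadlines, the DSUR list and the DSMB's SAE and SUSAR review meanwhile run on. At most about 4 of the 63–64 possible weeks at the maximum 6TG dose fall inside the general SAE window.

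The percentages measure calendar time and exposure, not harm missed; the documents give no rate of late unexpected reactions from which to estimate that. The conclusion assumes that sites follow the SAE section as worded. The sponsor should make the change: it concerns safety oversight and costs little. The point does not show that late toxicity goes unrecorded.

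**What to change.** Reconcile the AE/AESI, SAE, SUSAR, DSUR, DSMB and Recruitment and consent sections by amending the SAE section. From week 13 to end of therapy, in addition to SOS/VOD and NRH, investigators report within 24 h:

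1. any serious event suspected to be related to the study drugs and unexpected against the reference safety information, whether or not it is on the AESI list;
2. Hy's-law cases.

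Keep the exemption for expected toxicities, and say in the SAE section that the exemption covers expected events, as the AE section already does. State in the DSMB section that SAE counts outside the expedited categories cover weeks 1–12 only, so that later counts are not read as an absence of events. State in the DSUR section which source supplies expected serious reactions after week 12. Align the sentence on continuous CRF registration with the 12-week limit on general AE recording. If the parent protocol already contains a SUSAR route, a cross-reference and removal of the conflicting wording may be enough for item 1.

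The cost is a short amendment, site notification and a modest number of extra reports. The analysis and sample size are not affected.

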#### Suspected unexpected serious adverse reactions (SUSARs)

Unexpected adverse reactions are SUSARs, if the following three conditions are met:The event must be serious.There must be a certain degree of probability that the event is a harmful and an undesirable reaction to the medicinal product under investigation, regardless of the administered dose.The adverse reaction must be unexpected, that is to say the nature and severity of the adverse reaction are not in agreement with the product information as recorded in:Summary of Product Characteristics (SmPC) for an authorized medicinal product.Investigator’s Brochure for an unauthorized medicinal product.

The sponsor will promtly forward via e-mail the SUSAR to the National Principle Investigator and/or Clinical Trial Unit (CTU) where the SUSAR occurred. The applicable country will report the SUSAR to the National Compent Authorities, web portal Eudravigilance and institutional review borad/ethics committee (IRB/EC) if applicable. In addition, the sponsor will promptly notify all NPIs/CTUs about a SUSAR. The sponsor has to report the SUSAR promptly to the NPIs/CTUs to enable the country to comply with the regulatory requirements and timelines for SUSAR reporting. The timeline to report the SUSAR is 7 days of first knowledge of the SUSAR that result in death or are life threatening followed by a period of maximum of 8 days to complete the initial preliminary report. All other SUSARS will be reported within a period of maximum 15 days after the sponsor has first knowledge of the SUSAR.

SUSARs are recorded in an overview list (line-listing) that will be submitted once every year to the accredited regulatory authorities. This line-listing provides an overview of all SUSARs from the study medicine, accompanied by a brief report highlighting the main points of concern.

#### Developmental safety update report (DSUR)

In accordance with the ALLTogether1 protocol, the sponsor will submit a safety report to the NPI/CTU in the participating countries once a year throughout the clinical study, to enable them to report the DSUR to the accredited IRB/EC, and competent authorities of the participating countries.

This safety report consists of:A list of all suspected (unexpected or expected) serious adverse reactions, along with an aggregated summary table of all reported serious adverse reactions, ordered by organ system.A compilation of AESIs for the whole patient-population and the pooled patient-populations for the risk-groups and for the randomized studies.A report concerning the safety of the subjects, consisting of a complete safety analysis and an evaluation of the balance between the efficacy and the harmfulness of the interventions under investigation.

The data in the annual progress and safety report is aggregated without specification of randomized arms.

#### Follow-up of adverse events

All AEs during the TEAM study will be followed annually until they have abated, or until a stable situation has been reached. Depending on the event, follow up may require additional tests or medical procedures as indicated, and/or referral to a general physician or a medical specialist.

#### Data safety monitoring board (DSMB)

The DSMB for the TEAM study will be the same as for the ALLTogether1 protocol. The DSMB periodically (at least annually) reviews safety and study data and makes recommendations based on their review along with assessing the performance of overall study operations and any other relevant issues, as necessary. The basis for the review is a report provided by the study statistician without the knowledge or influence by the sponsor, PI or steering committee. The DSMB will receive annual progress reports on patient recruitment, rate of events (relapse, DCR1 and SMN), occurrences of SOS, NRH, AESI, SAEs, SUSARs and levels of DNA-TG in the randomization arms.

The DSMB can recommend extension of the study to ensure adequate enrollment.

The advice of the DSMB will be sent to the sponsor of the study to be shared with the steering committee. Should the sponsor decide not to fully implement the advice of the DSMB, the sponsor will send the advice to the reviewing accredited competent authorities, including a note to substantiate why (a part of) the advice of the DSMB will not be followed.

### Statistical analysis

#### Sample size calculation

Historic data was pooled from four of the study-groups (UKALL, DCOG, COALL and NOPHO) of patients with positive EOI MRD-values consistent with the IR-group. This group was, by way of threshold analysis, sub-divided into an IR-Low and an IR-High risk group. The IR-high risk group was considered to have an unacceptably low 5-year DFS due to relapses (0.844), after consideration of events before the protocol time for the TEAM randomization (9 months).

#### Outcome assumptions

The TEAM- and InO sub-protocols (that run in parallel) are regarded as fully independent experiments. For each of the two studies the outcome of the experimental intervention will be compared to the control arm, but comparisons between the two experimental arms will not be made. The patient numbers and power calculations are based on:United Kingdom will not provide patients to the TEAM study.French centers will join the ALLTogether1 protocol from October 2021.There will be an 80% participation rate of all eligible patients for the TEAM study.Patient accrual will be uniform over the 5 years accrual period.24% of randomized patients have T-ALL.50% are randomized to the experimental TEAM for both T- and BCP-ALL.The 5-years DFS for control BCP-ALL patients is 84% and for T-cell ALL it is 81%.

The primary endpoint is DFS, where we aim to show an improvement in the 5-year rate from 84 to 91% for BCP-patients (HR 0.54) and 81 to 87% (HR 0.61) for T-cell ALL compared to standard maintenance. A minimum of 778 randomized patients would be appropriate to assess this improvement with 80% power and a 2-sided 5% alpha. With 878 patients recruited over 5 years (assuming 39% are IR-high and 80% accept randomization), an additional 5 years follow-up, a 2-sided 5% alpha we will have 84% power to detect this difference.

Recruitment into R3 – TEAM will be discontinued after 778 patients have been randomized and found to be evaluable. Since power has been calculated for a 5-year recruitment time and a minimum of 2 years follow-up time for the last recruited patient, the follow-up time will be extended if the recruitment time is significantly shorter than 5 years.

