**Methods:**

TEAM is a randomized phase 3 sub-protocol to the ALLTogether1 trial, which includes patients 0–45 years of age with newly diagnosed B-cell precursor or T-cell ALL, and stratified to the intermediate risk-high (IR-high) group, in 13 European countries. In the TEAM trial, the traditional methotrexate (MTX)/6-mercaptopurine (6MP) maintenance backbone (control arm) is supplemented with low dose (2.5–12.5 mg/m^2^/day) oral 6-thioguanine (6TG) (experimental arm), while the starting dose of 6MP is reduced from 75 to 50 mg/m^2^/day. A total of 778 patients will be included in TEAM during ~ 5 years. The study will close when the last included patient has been followed for 5 years from the end of induction therapy. The primary objective of the study is to significantly improve the disease-free survival (DFS) of IR-high ALL patients by adding 6TG to 6MP/MTX-based maintenance therapy. TEAM has 80% power to detect a 7% increase in 5-year DFS through a 50% reduction in relapse rate. DFS will be evaluated by intention-to-treat analysis. In addition to reducing relapse, TEAM may also reduce hepatotoxicity and hypoglycemia caused by high levels of methylated 6MP metabolites. Methotrexate/6MP metabolites will be monitored and low levels will be reported back to clinicians to identify potentially non-adherent patients.

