## Discussion

TEAM is a novel approach for maintenance therapy, that is based on a line of supportive studies relating to anticipated toxicity [25, 32], a large observational study on the association between DNA-TG and relapse risk [20], and a pilot study on feasibility and efficacy (with respect to DNA-TG) of the TEAM drug combination [23].

However, only this large randomized trial can determine the efficacy with respect to reduction of relapse risk, and toxicity of the drug combination. Both SOS/NRH and SMN are potential risk factors. The risk of SOS and NRH is anticipated to be low, due to the low dose of 6TG used [32]. Furthermore, SOS has not been associated with DNA-TG [25]. SMN has been associated with higher doses and longer duration of 6MP therapy in previous retrospective studies [36]. An IPD meta-analysis including 1910 patients, of which 14 developed a SMN, did not find an association between DNA-TG and SMN, although larger studies confirming this are warranted [22].

In addition, the risk of infections and osteonecrosis has been considered. However, DNA-TG is not associated with degree of neutropenia [20]; and although most osteonecrosis occur during MT, MTX and 6MP metabolites have not been associated with this complication [37].

The monitoring of MTX and thiopurine metabolites, with reporting back to clinicians on low measures indicating potential non-adherence, may increase treatment adherence in both treatment arms.

We aim to show an improvement in the 5-year DFS from 84 to 91% for BCP-patients (HR 0.54) and 81 to 87% (HR 0.61) for T-cell ALL compared to standard maintenance, through a 50% reduction in relapse rate. The randomization of 778 patients yields a 80% power and a 2-sided 5% alpha to assess this improvement.

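### The T-ALL hazard ratio does not match its own DFS target (81% to 87% is HR 0.66, not 0.61), so the target and the power statement need reconciling on one named follow-up basis

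*Protocol article*

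**What the plan says.** Outcome assumptions sets separate targets by immunophenotype. For BCP-ALL it is an "improvement in the 5-year rate from 84 to 91% for BCP-patients (HR 0.54"); for T-ALL it is "81 to 87% (HR 0.61) for T-cell ALL compared to standard maintenance". The control rates are restated in the list of assumptions: "The 5-years DFS for control BCP-ALL patients is 84% and for T-cell ALL it is 81"%. The mix is given as "24% of randomized patients have T-ALL", with equal allocation and uniform accrual over 5 years.

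Two power figures follow. The first is "A minimum of 778 randomized patients would be appropriate to assess this improvement with 80% power and a 2-sided 5% alpha". The second, for 878 patients, reads "an additional 5 years follow-up, a 2-sided 5% alpha we will have 84% power to detect this difference". The next paragraph says that power was worked out for 5 years' recruitment and at least 2 years' follow-up of the last patient.

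The Discussion repeats the T-ALL pair: "81 to 87% (HR 0.61) for T-cell ALL compared to standard maintenance, through a 50% reduction in relapse rate". The Abstract (Methods) summarises: "TEAM has 80% power to detect a 7% increase in 5-year DFS through a 50% reduction in relapse rate".

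Analysis of endpoints specifies a Cox model with a Wald test for the primary comparison. Main study endpoint names the 5-year probability of DFS.

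**The concern.** Each immunophenotype has a control rate, a target rate and a hazard ratio. Under proportional hazards any two fix the third. The BCP triple is consistent and the T-ALL triple is not, so two different T-ALL effects are stated as the design target, and this occurs in two places.

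At stake is which effect the 80% power belongs to. If 0.61 was used, the quoted power refers to a somewhat larger T-ALL effect than the 81% to 87% that the trial says it aims to show. The text also gives more than one follow-up basis, so a reader cannot settle the question from the article.

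**Working it through.** **Step 1: hazard ratios.** Under proportional hazards HR = ln(S_exp)/ln(S_ctl).

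- BCP: ln(0.91)/ln(0.84) = 0.541. The printed 0.54 is reproduced, so this is the conversion in use.
- T-ALL: ln(0.87)/ln(0.81) = 0.661. The article prints 0.61.
- In reverse: 0.81^0.61 = 0.879, and ln(0.88)/ln(0.81) = 0.607. HR 0.61 is therefore what an 88% target would give.
- Rounding: the extremes of 80.5–81.5% to 86.5–87.5% are ln(0.875)/ln(0.805) = 0.616 and ln(0.865)/ln(0.815) = 0.709. The value 0.61 lies outside.
- Other measures: the risk ratio is 0.13/0.19 = 0.68, and the odds ratio is (0.13/0.87)/(0.19/0.81) = 0.64. Neither is 0.61.

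**Step 2: power on the basis the article names.** Inputs from Outcome assumptions: N = 778 or 878, 76% BCP and 24% T-ALL, 1:1, uniform 5-year accrual, minimum 2 years' follow-up, two-sided 5%. Assumptions not in the article: constant hazards, no dropout, Schoenfeld's formula.

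With L = −ln(S5)/5, the event probability over follow-up of 2 to 7 years is P = 1 − [exp(−2L) − exp(−7L)]/(5L). Events D are summed over arms and immunophenotypes. Power = Φ(√(D/4) × m − 1.96), where m is the event-weighted mean of |ln HR|.

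The printed HRs (0.54/0.61) at N = 778:

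- BCP: P = 0.144 and 0.081, giving 66.5 events.
- T-ALL: P = 0.171 and 0.109, giving 26.1 events.
- D = 92.7 and m = 0.582, so √(D/4) × m = 2.80 and power = 80.0%.

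The printed percentages (0.541/0.661) at N = 778:

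- BCP: 66.6 events.
- T-ALL: P = 0.171 and 0.117, giving 26.9 events.
- D = 93.5 and m = 0.557, so √(D/4) × m = 2.69 and power = 76.8%.

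| N | Stated power | HRs 0.54/0.61 | Percentages (0.541/0.661) |
|---|---|---|---|
| 778 | 80% | 80.0% | 76.8% |
| 878 | 84% | 84.5% | 81.6% |

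**Step 3: other hazard shapes and formulas** (N = 778, HR 0.661, same 5+2-year basis).

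- Weibull shape 0.8 to 0.5 (front-loaded): 77.4% to 78.5%.
- Constant hazard to year 5, then none: 73.3%.
- Constant hazard to year 3, then none: 79.7%.
- Freedman's formula, constant hazard: 74.5% (77.6% with HR 0.61).

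**Step 4: a route that keeps 87%.** Pooled 5-year DFS is 0.76 × 0.84 + 0.24 × 0.81 = 0.833 in controls and 0.76 × 0.91 + 0.24 × 0.87 = 0.900 in the experimental arm. A two-sided 5% comparison of these proportions gives 79.3% at 778 and 83.9% at 878. With 88% for T-ALL it gives 82.3% and 86.6%. The Abstract's 7% does not separate the two readings: the pooled gain is 6.8 points with 87% and 7.0 points with 88%.

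**Step 5: longer minimum follow-up** (formula of step 2, N = 778, HR 0.661).

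| Minimum follow-up | Power |
|---|---|
| 2 years | 76.8% |
| 2.5 years | 80.7% |
| 3 years | 84.0% |
| 4.25 years | 90.1% |
| 5 years | 92.6% |

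The later rows assume that the hazard stays constant beyond year 5, which is optimistic.

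**The case against.** The mismatch itself has no defence. The power consequence does.

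The article names no power formula, hazard shape or dropout rate. Step 4 shows that the percentages alone, compared as 5-year proportions, come within a point of both published powers. On that route 0.61 would be a misprinted annotation that never touched the sample size. Two things weaken this explanation without excluding it: the article says power was calculated for a 2-year minimum follow-up, and the planned test is a Cox Wald test.

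The follow-up basis is also unsettled. Outcome assumptions attaches 5 further years to the 84% figure and then gives 2 years as the minimum. The Abstract, Study design and the end-of-study section allow the study to run until 5 years from the last patient's end of induction. Randomization comes at about 9 months (Sample size calculation), and remission is implied at about 1 month (Maintenance therapy equates 2 years from remission with 25 months from diagnosis). Minimum follow-up could therefore reach about 60 − 8 = 52 months, or 4.3 years. A literal 5-year minimum gives 92.6% and 95.1% for 778 and 878 patients, so it cannot be the source of the published figures, but it does show that longer follow-up recovers the loss.

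A reader might infer that 80% is attainable only with the wrong HR, that the trial has 77% power without qualification, or that it must recruit more (about 843 patients would give 80% on the 5+2-year basis). The documents support none of these: the source of the 80% is not stated, and 77% applies only to an analysis at 2 years' minimum follow-up under the assumptions of step 2.

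**Conclusion.** The T-ALL hazard ratio and the T-ALL target contradict each other in Outcome assumptions and in the Discussion. This is plain arithmetic, depends on no modelling choice and is certain: 81% to 87% is 0.66, and 0.61 belongs to about 88%.

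That the wrong value entered the power is a reasonable inference, because both published figures reproduce with 0.61 on the named 5+2-year basis under constant hazards and Schoenfeld. It is not proved. If it did enter, the cost on that basis is about 3 points (80.0% to 76.8% at 778; 84.5% to 81.6% at 878), and half a year more of minimum follow-up would restore it under constant hazards. This is a moderate correction; it does not show that the design is inadequate.

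**What to change.** 1. In Outcome assumptions and the Discussion, change the T-ALL hazard ratio to 0.66, or change the target to 88% if HR 0.61 was intended. The sponsor should confirm which value went into the calculation.
2. Reconcile the follow-up basis: the 2-year minimum and the additional 5 years in Outcome assumptions, and the study end in the Abstract, Study design and the end-of-study section.
3. Restate the power of 778 patients for the corrected target, naming the follow-up basis and the assumed hazard shape. If 87% stands, constant hazards give about 77% at 2 years' minimum follow-up, about 81% at 2.5 years, and more beyond that. Bring the 878-patient figure and the Abstract into line.

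The cost is wording and one re-run of the power calculation. Sample size, test, alpha and trial conduct are unchanged, and no event-driven redesign is needed.
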